## **9.6 Milestones**

Table 9.1 shows the project milestones. Six-monthly reports will be submitted to the funder during the duration of the trial and the final report will be submitted at month 45. Other reports may be requested by the funder and will be submitted on request.

Table 9.1 Milestones

| Year one (Nov 2017-Oct 2018)     |         |                                                                                                                                                                                                                                                                                                                                                  |
|----------------------------------|---------|--------------------------------------------------------------------------------------------------------------------------------------------------------------------------------------------------------------------------------------------------------------------------------------------------------------------------------------------------|
| By month 3                       | Jan 18  | Construct database, web-based data entry system, randomisation program
Establish first six centres (R&D negotiations, appoint local recruitment officers).
Collaborator agreements signed off
First TSC and DMEC (Joint)
Focus group with Women's Voices completed and analysed                                                      |
| By month 6                       | Apr 18  | Staff training and teaching materials finalised. Study documents printed.
Centre visits at first six centres. Ready to start recruitment at first six centres                                                                                                                                                                                 |
| By Month 9                       | Jul 18  | Recruitment open in six pilot centres with 18 women randomised
Record six to nine recruitment sessions
Record five self-management teaching appointments
Start recruitment of randomised women to interview study
Start recruitment of non-randomised women to interviews                                                            |
| By Month 12                      | Oct 18  | Ten centres active and 75 women randomised (63 women from pilot centres and 12 women from additional centres)
Record 12-18 recruitment sessions
Undertake interviews with recruiters in each pilot centre
First annual report to funders
Complete analysis of recording data to support recruitment
Complete internal pilot study |
| Year Two (Nov 2018 – Oct 2019)   |         |                                                                                                                                                                                                                                                                                                                                                  |
| By month 15                      | Jan 19  | 14 centres active 133 women randomised
Complete recruitment with women who decline randomisation
Second DMEC and second TSC
HTA provided with all information about internal pilot (including TSC and DMEC advice) and decision made regarding the best course of action                                                                |
| By month 18                      | Apr 19  | 17 centres active 229 women randomised                                                                                                                                                                                                                                                                                                           |
| By Month 21                      | July 19 | 36 randomised women recruited for interview study                                                                                                                                                                                                                                                                                                |
| By month 24                      | Oct 19  | Second annual report to funders
Interviews commence with healthcare professionals in recruiting centres
30 self-management teaching appointments recorded                                                                                                                                                                                  |
| Year Three (Nov 2019 – Oct 2020) |         |                                                                                                                                                                                                                                                                                                                                                  |
| By month 27                      | Jan 20  | Recruitment complete in centres (n=330 women randomised)                                                                                                                                                                                                                                                                                         |
| By month 33                      | Jul 20  | Questionnaire follow up at six months after randomisation completed
Complete data collection with women who decline randomisation                                                                                                                                                                                                             |

|             |        |                                                            |
|-------------|--------|------------------------------------------------------------|
| By month 36 | Oct 20 | Third annual report to funders
Third DMEC and third TSC |
|-------------|--------|------------------------------------------------------------|

#### **Year Four (Jan 2021 – Jan 2022)**

|             |        |                                                                                                                                                                                                                                      |
|-------------|--------|--------------------------------------------------------------------------------------------------------------------------------------------------------------------------------------------------------------------------------------|
| By month 39 | Jan 21 | Questionnaire follow up at 12 months completed

Interview follow up with women at 18 months complete (by March 21)
Interviews complete with healthcare professionals in recruiting centres                                  |
| By month 45 | Jul 21 | Questionnaire follow up at 18 months complete                                                                                                                                                                                        |
| By Month 47 | Sep 21 | All data cleaning complete and database lock                                                                                                                                                                                         |
| By Month 50 | Dec 21 | End of study DMEC and TSC meeting
All centres closed down                                                                                                                                                                         |
| By Month 51 | Jan 22 | Complete RCT analysis
Complete Process evaluation analysis (all data sources)
Complete Health Economic analysis
Data archiving and arrangements for long term follow-up
Dissemination – including final report to funder |

## **9.7 Finance**

The trial is supported by a grant from the NIHR Evaluation, Trials and Studies Coordinating Centre (NETSCC), Health Technology Assessment (HTA) Programme (HTA 16/82/01).

## **9.8 Confidentiality**

All paper records will be kept in a secure storage area with limited access. The investigators and study centre staff involved with this study will not disclose or use for any purpose other than performance of the study, any data, record, or other unpublished, confidential information disclosed to those individuals for the purpose of the study.

Computers used to collate the data will have limited access measures via user names and passwords. Published results will not contain any personal data that could allow identification of individual participants.

## **9.9 Data Protection**

All investigators and study centre staff involved with this study will comply with the requirements of the General data Protection Regulation (GDPR) and the Data Protection Act 2018 with regard to the collection, storage, processing and disclosure of personal information. Access to collated participant data will be restricted to individuals treating the women, representatives of the sponsor(s) and representatives of regulatory authorities.

## **10. SAFETY REPORTING**

Collaborators and participants may contact the Chair of the TSC through the TOPSY Study Glasgow Office about any concerns they may have about the trial. If concerns arise about procedures, participants or clinical or research staff (including risks to staff) these will be relayed to the Chair of the DMEC.

As the trial group to which participants are allocated cannot be masked from the participants or the centre staff after randomisation has occurred, unblinding is not an issue in this trial.

All women in the TOPSY study have had a vaginal pessary inserted. As a foreign body placed in the vagina, this is recognised as a potential cause of specific symptoms e.g. bleeding and vaginal ulceration/erosion.

Expected events arising from pessary treatment are noted below and thus will NOT be collected as adverse events but will be recorded:

- Granulation of vaginal tissue
- Involuntary expulsion of pessary
- Vaginal smell
- Vaginal discharge
- Bleeding during pessary change.

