**Adverse Reaction (AR)**

Any untoward and unintended response that has occurred due to the intervention.

- Symptomatic and treated UTI (treated by HCP)
- Confirmed or suspected vaginal infection requiring time without pessary
- New or worsening urinary incontinence.
- New or worsening voiding dysfunction (except urinary retention requiring medical intervention)
- New or worsening defaecation dysfunction (except impaction requiring hospital intervention)
- Unscheduled vaginal bleeding
- Vaginal erosion or ulceration diagnosed by a healthcare professional and requiring time without the pessary
- Pain or irritation in the vagina or lower abdomen in the absence of infection
- New or worsening dyspareunia
- Vaginal fibrosis or constriction ring

For the purpose of the TOPSY study we will record any AEs that require the study participant to seek advice from a healthcare professional (e.g. common colds dealt with at home will not be reported) and which are NOT expected events of having a vaginal pessary as previously outlined.

A **serious adverse event (SAE), or Serious Adverse Reaction (SAR)** is any AE or AR which

- results in death;
- results in persistent or significant disability or incapacity;
- is life threatening (i.e. the subject was at risk of death at the time of the event; it does not refer to an event which hypothetically might have caused death if it were more severe);
- requires in-patient hospitalisation or prolongation of existing hospitalisation.

**Serious adverse events** potentially associated with a pessary include:

- Pessary entrapment in the vagina requiring removal in theatre
- Urinary retention requiring catheterisation
- Faecal impaction requiring hospital intervention
- Fistula: recto-vaginal or vesico-vaginal.

- Vaginal cancer
- Ureteric obstruction

Note: Hospitalisations for treatment planned prior to randomisation will not meet SAE criteria. Any hospitalisation post randomisation, will be recorded.

Pregnancy is not considered an AE or SAE, however if a woman becomes pregnant during the trial, they will be withdrawn from the study and pessary care advice would be given according to local standard care. This would be recorded on a TOPSY study change of status form.

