#### **10.1.1 Detecting AEs, ARs SAEs and SARs**

All adverse events (including adverse reactions, serious adverse events and unexpected) must be recorded from the time a participant signs the consent form to take part in the study until the last follow up (18 months). (Expected events from having a pessary are recorded on study specific CRF's and not recorded as additional AEs).

In the standard care group, the local TOPSY research team will ask about the occurrence of AEs/SAEs at every pessary follow up appointment. Open-ended and non-leading verbal questioning of the participant will be used to enquire about AE/SAE occurrence. Participants will also be asked if they have been admitted to hospital, had any accidents, used any new medicines or changed medication regimens. If there is any doubt as to whether a clinical observation is an AE, the event should be recorded. Women in the self-management group are asked during the teaching appointment and advised in the information leaflet to call the telephone helpline if they experience any of the symptoms that may be indicative of an SAE/AE. The Pessary complication questionnaire completed by all women at all time-points will also capture any adverse events experienced.

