### **10.1.3 Assessment of AEs and SAEs**

Each AE must be assessed for seriousness, causality, severity and expectedness by the local PI or another suitably qualified physician in the local TOPSY research team who is trained in recording and reporting AEs and who has been delegated this role.

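### The exemption of five expected pessary events from adverse-event collection has no seriousness limit, conflicts with the protocol's AE and SAE definitions, and nothing says which prevails

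*Protocol*

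**What the plan says.** All references are to the protocol.

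- **The exemption.** Section 10 lists granulation of vaginal tissue, expulsion of the pessary, smell, discharge and "Bleeding during pessary change", under the rule "Expected events arising from pessary treatment are noted below and thus will NOT be collected as adverse events but will be recorded". Section 10.1, after the adverse-reaction list, repeats it: the AEs to be recorded are those that lead the woman to seek professional advice and "which are NOT expected events of having a vaginal pessary as previously outlined". Section 10.1.1 gives the destination: "Expected events from having a pessary are recorded on study specific" CRFs, not the AE record.
- **The definitions.** Section 10.1 defines an AE as any untoward medical occurrence in a participant, whether or not caused by the intervention, and makes no exception. An SAE or SAR "is any AE or AR which" meets one of four criteria. One of them is that it "requires in-patient hospitalisation or prolongation of existing hospitalisation". A note to this definition sets aside admissions planned before randomisation and adds: "Any hospitalisation post randomisation, will be recorded".
- **The route.** Section 10.1.2 has the SAE form completed when an AE is serious. Section 10.1.3 says "Each AE must be assessed for seriousness, causality, severity and expectedness by the local PI" or a delegated physician. Section 10.2 requires the local PI to report to the study office within 24 hours of becoming aware of an SAE.

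**The concern.** The exemption works by event name alone. It sets no threshold of severity or seriousness, and no sentence brings a listed event back into the AE/SAE route once it becomes serious. Expectedness is thus applied as a filter before seriousness has been judged, although 10.1.3 treats the two as separate judgements on each AE.

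Two of the five events, expulsion and bleeding at a change, bear directly on pessary handling, which the self-management arm moves from the clinic to the home. If centres read the rule differently, the SAE record depends partly on the reader. That record feeds the 24-hour reports and, under Section 9.5, the serious events put before the DMEC.

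**Working it through.** No arithmetic applies. The check is to follow one event, a bleed during a pessary change that leads to an unplanned in-patient admission after randomisation, through the text under each rule.

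**Under the exemption (Section 10, repeated in 10.1 and 10.1.1)**
1. The event is on the list by name, so it is not collected as an AE and goes to a study-specific CRF.
2. The SAE form (10.1.2) is triggered by an AE that meets a seriousness criterion. No AE has been recorded.
3. The seriousness assessment (10.1.3) applies to each AE, so it is not called for.
4. A centre following this chain has no SAE to report under 10.2.

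**Under the definitions (10.1)**
1. The event is an untoward medical occurrence, so it is an AE.
2. It required admission, so it meets a seriousness criterion and is an SAE.
3. The 24-hour duty in 10.2 starts when the PI becomes aware of an SAE. It does not depend on an AE form having been filed.

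The two chains give opposite results for the same event, and each follows from the text. Three further points bear on whether the protocol resolves the conflict.

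- **The hospitalisation note.** It sits within the SAE definition and makes no exception for listed events, which favours the second chain. But the verb it uses, recorded, is the one Section 10 uses for events that are expressly not collected as AEs. So it does not settle whether such an admission is assessed for seriousness or reported within 24 hours. It also covers only admission, one of the four criteria.
- **Severity limits elsewhere.** In the adverse-reaction list, voiding dysfunction excludes retention needing medical intervention, and defaecation dysfunction excludes impaction needing hospital intervention. Retention requiring catheterisation and impaction requiring hospital intervention then appear in the SAE list. The protocol therefore separates the serious form of an event from the ordinary form where it chooses to, and does not do so for the five listed events.
- **Where expectedness is already used.** In 10.2 the 15-day report to the ethics committee, sponsor and DMEC is for events judged related and unexpected. Expectedness has its place there, after seriousness. Nothing in the reporting scheme needs it as an earlier filter.

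**The case against.** The best defence is that Section 10 is a collection rule and does not redefine an AE. The sentence in 10.1 that excludes expected events can be read as treating them as AEs that are not separately recorded. On that reading a serious listed event is an SAE by definition, and the PI who learns of it must report it. Section 10.1.1 also requires all AEs, including SAEs, to be recorded, and tells centres to record in case of doubt. Unscheduled vaginal bleeding is listed separately as an adverse reaction, as are infection and ulceration.

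Much of this stands. A reader might infer that a serious listed event can never enter the SAE route, or that it would be missing from the trial's safety conclusion. The documents support neither reading. The route is ambiguous, not closed. Listed events are recorded on CRFs, both arms complete the complications questionnaire at every time-point, and under Section 9.5 the DMEC can ask for further analyses.

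The defence still does not remove the conflict. The instruction on doubt is little help for an event that is on the exclusion list by name. The text does not say whether a serious bleed at a change counts as the adverse reaction or as the exempt event. The question about hospital admission in 10.1.1 is described within standard-care visits, while women who self-manage are asked to phone, so it is not clearly a safeguard in both arms.

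Timing also limits the remedy. This is version 11, of November 2022, and Table 9.1 has 18-month follow-up complete by July 2021 and the database locked by September 2021. New wording cannot change how main-trial events were handled. It can still matter for the 4-year follow-up: there, staff screen questionnaires for possible SAEs, and Appendix D otherwise keeps Section 10 as it is.

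**Conclusion.** The point holds as an unresolved conflict between stated rules. The exemption in Sections 10, 10.1 and 10.1.1 has no seriousness limit, the SAE form and seriousness assessment are written for AEs, and the definitions and hospitalisation note in 10.1 point the other way. Centres could each follow the text and still treat the same serious event differently.

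Its reach is any occurrence of the five named events that meets a seriousness criterion. The documents give no rate for these, so no number of affected events can be stated, and the finding does not need one. What is at risk is SAE classification and 24-hour reporting. The underlying data are held elsewhere and could be reclassified. The conclusion rests on the protocol text alone and assumes that centres had no separate instruction, such as SAE form guidance, that already settles the matter.

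**What to change.** Reconcile Sections 10, 10.1 and 10.1.1 with one sentence: the exemption covers only non-serious occurrences, and any listed event that meets a seriousness criterion in 10.1 follows the SAE route in 10.2, with expectedness judged afterwards. Put the same sentence in the centre guidance and apply it to the questionnaire review under Appendix D, Section 10.

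For the main trial, have the study office check the CRFs already returned, including the recorded hospitalisations, for listed events that met a criterion, and classify any found as SAEs for the DMEC and the safety report.

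The cost is a short amendment, a short CRF check and possibly a few more SAE forms. No change to the design, sample size or efficacy analysis is needed.

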### **10.1 Procedure for reporting AEs and SAEs in TOPSY**

#### **DEFINITIONS**

##### **Adverse Event (AE)**

Any untoward medical occurrence in a study participant, which does not necessarily have a causal relationship with the study intervention.

**Adverse Reaction (AR)**

Any untoward and unintended response that has occurred due to the intervention.

- Symptomatic and treated UTI (treated by HCP)
- Confirmed or suspected vaginal infection requiring time without pessary
- New or worsening urinary incontinence.
- New or worsening voiding dysfunction (except urinary retention requiring medical intervention)
- New or worsening defaecation dysfunction (except impaction requiring hospital intervention)
- Unscheduled vaginal bleeding
- Vaginal erosion or ulceration diagnosed by a healthcare professional and requiring time without the pessary
- Pain or irritation in the vagina or lower abdomen in the absence of infection
- New or worsening dyspareunia
- Vaginal fibrosis or constriction ring

For the purpose of the TOPSY study we will record any AEs that require the study participant to seek advice from a healthcare professional (e.g. common colds dealt with at home will not be reported) and which are NOT expected events of having a vaginal pessary as previously outlined.

A **serious adverse event (SAE), or Serious Adverse Reaction (SAR)** is any AE or AR which

- results in death;
- results in persistent or significant disability or incapacity;
- is life threatening (i.e. the subject was at risk of death at the time of the event; it does not refer to an event which hypothetically might have caused death if it were more severe);
- requires in-patient hospitalisation or prolongation of existing hospitalisation.

**Serious adverse events** potentially associated with a pessary include:

- Pessary entrapment in the vagina requiring removal in theatre
- Urinary retention requiring catheterisation
- Faecal impaction requiring hospital intervention
- Fistula: recto-vaginal or vesico-vaginal.

- Vaginal cancer
- Ureteric obstruction

Note: Hospitalisations for treatment planned prior to randomisation will not meet SAE criteria. Any hospitalisation post randomisation, will be recorded.

Pregnancy is not considered an AE or SAE, however if a woman becomes pregnant during the trial, they will be withdrawn from the study and pessary care advice would be given according to local standard care. This would be recorded on a TOPSY study change of status form.

